#### 34–36 weeks’ gestation appointment

Metformin will be dispensed to those allocated the drug. Women will be instructed to stop trial medication on the day of delivery and will be asked to hand in the rest of the trial medication to the research team. Information on any side effects and adverse events will be collected in the metformin arm. Adherence will be assessed by tablet count. Information on pregnancy complications will be collected and weight will be recorded in all arms.

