##### Standard care

Women randomised to the standard care group will attend all study visits except the 8 weekly intervention sessions and receive routine antenatal care according to local health care provision.

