#### 22–25 weeks’ gestation appointment

All participants will be fitted with a continuous glucose monitoring (CGM) sensor for 7–10 days, again in blinded mode. Dietary intake and physical activity will be assessed using the FFQ and accelerometer. In the ‘lifestyle plus metformin’ arm, metformin will be dispensed, information on any side effects or adverse events will be collected and adherence will be assessed by tablet count.

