### Data monitoring

A trial steering committee will be established to oversee the conduct and progress of the trial. The terms of reference of the Trial Steering Committee have been developed separately.

All adverse events (AEs) and serious adverse events (SAEs) will be recorded from the time a participant is randomised into the trial. All SAEs, serious adverse reactions (SARs) or unexpected serious adverse reactions (SUSARs) in the lifestyle and metformin arm will be reported immediately by the chief investigator to the King’s Health Partners Clinical Trial Office (KHPs-CTO) in accordance with the current Pharmacovigilance Policy.

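### The visit procedures seek adverse events only in the lifestyle plus metformin arm, which does not fit the rule that all adverse events are recorded from randomisation

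*Protocol article*

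**What the plan says.** The general rule is in the article's Data monitoring section: "All adverse events (AEs) and serious adverse events (SAEs) will be recorded from the time a participant is randomised into the trial". It has no arm restriction.

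The visit procedures are narrower:

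- **22–25 weeks' gestation appointment:** "In the ‘lifestyle plus metformin’ arm, metformin will be dispensed, information on any side effects or adverse events will be collected". The opening words of that sentence limit everything in it to one arm.
- **24–28 weeks' gestation appointment:** no adverse event enquiry is mentioned for any arm.
- **34–36 weeks' gestation appointment:** "Information on any side effects and adverse events will be collected in the metformin arm". Two sentences later the same section says "Information on pregnancy complications will be collected and weight will be recorded in all arms".

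On attendance, the Standard care section says "Women randomised to the standard care group will attend all study visits except the 8 weekly intervention sessions".

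On serious events, the sentence after the general rule says that those "in the lifestyle and metformin arm will be reported immediately by the chief investigator" to the clinical trial office.

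**The concern.** An adverse event count depends on whether and how women are asked. If one arm is asked at study visits and the others are not, the recorded rates differ even when the true rates are equal. Symptoms that also occur in pregnancy without any drug are the most exposed, because they tend to be recorded only when someone asks.

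The trial is open label for participants and research staff, so reporting is already open to influence by knowledge of allocation. Unequal enquiry adds a second source of difference in the same direction. At stake is whether the pilot can give a background rate of general adverse events against which the metformin arm can be read. The pilot is meant to inform a larger trial of these interventions.

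**Working it through.** The document states no figure on this point, so the check is a comparison of text, followed by an illustration under a stated assumption.

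**Step 1: the rule against the visits.**

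| Place in the article | Whose adverse events |
|---|---|
| Data monitoring, general rule | All randomised women |
| 22–25 week visit | Lifestyle plus metformin arm |
| 24–28 week visit | None mentioned |
| 34–36 week visit | Metformin arm |

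Both visits that mention collection restrict it to one arm. Neither these sections nor Data monitoring gives a visit or method for the other two arms.

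**Step 2: is the restriction only loose wording?** The 34–36 week section separates items for the metformin arm from items for all arms within one paragraph, and it places adverse events in the first group. Both visit sections name adverse events as well as side effects, so the restriction is not confined to drug-specific symptoms. As written, it reads as intended.

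**Step 3: could the other arms be asked?** Yes. Standard care women attend all study visits apart from the weekly sessions, so the opportunity already exists.

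**Step 4: how many women are involved?** Planned recruitment is 84 (Sample size calculation and loss to follow-up), allocated 1:1:1. That gives 84 / 3 = 28 women in the arm with stated enquiry and 84 − 28 = 56 in the arms without it.

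**Step 5: direction and size.** Let p be the risk recorded under visit enquiry, equal in all arms. Let c be the fraction of those events that is recorded where no visit enquiry is made.

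- Recorded risk with metformin: p
- Recorded risk in the other arms: c × p
- Apparent risk ratio: p / (c × p) = 1/c
- Apparent risk difference: p × (1 − c)

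The document gives neither p nor c. For assumed values of c:

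| c | Apparent risk ratio, 1/c |
|---|---|
| 1.00 | 1.0 |
| 0.75 | 1.33 |
| 0.50 | 2.0 |
| 0.25 | 4.0 |

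For any c below 1 the ratio exceeds 1, so the direction is towards more recorded events with metformin. The size depends wholly on c, and the risk difference also on p. Neither can be derived from the document.

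**Step 6: what is not affected?** Pregnancy complications are collected in all arms at 34–36 weeks. Late-pregnancy, labour, delivery and neonatal data come from medical records with no arm restriction (Data management). The gap therefore concerns general, non-obstetric events and symptoms.

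**The case against.** The strongest reply is that the Data monitoring rule governs, and that it covers every randomised woman. The article condenses a full protocol that is not shown, and methods of enquiry are commonly left to that document. A reader might infer from the visit sections that women in the other two arms are never asked, or that no adverse event data will exist for them. The article says neither, and under its general rule such events may still be recorded. This part of the reply stands. What remains is that the visit text, as stated, does not deliver the rule evenly. That is a conflict between stated passages, not an omitted detail.

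A second reply is that no harm follows, because adverse event rates by arm are not a listed objective or outcome and no between-arm test of them is planned. A reader might infer that the definitive trial will inherit a false tolerability signal. The article does not support that. What it passes forward is recruitment, retention, adherence, acceptability and the standard deviation of mean 24-hour glucose, and acceptability comes from interviews. The point is therefore limited to any description of adverse events by arm.

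Third, the serious-event sentence could be read as leaving serious events in standard care unrecorded. That goes too far. The sentence concerns immediate reporting, and the sentence before it covers recording for everyone. However, its arm label could mean the combined arm or both intervention arms, and standard care is outside it on either reading, so it needs clarifying.

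**Conclusion.** The concern holds in a limited form. The 22–25 and 34–36 week sections do not fit the general recording rule and must be reconciled with it. If the visit sections are followed as written, general adverse events are actively sought in about 28 of 84 women and not comparably in the other 56. Any by-arm description would then lean towards more events with metformin.

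The direction rests on one assumption: that events are recorded less completely where no visit enquiry is made. The size cannot be stated. A large excess in percentage points would require an assumed background rate and almost no recording in the other arms, and the general rule speaks against the latter. Obstetric, delivery and neonatal events are outside the problem. The full protocol may already settle the matter, but the article as it stands is inconsistent. The correction is worth making because it is cheap and improves the safety data.

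**What to change.** 1. **22–25 week section:** split the sentence. One part should say that adverse events are asked about in all three arms, with the same questions. The other should keep dispensing, tablet count and drug-specific side-effect questions in the lifestyle plus metformin arm. Merely replacing the arm label would not work, because that label also governs dispensing.
2. **34–36 week section:** amend it in the same way, with a common adverse event enquiry in all arms and drug-specific questions added for metformin only.
3. **Data monitoring section:** state which arms the serious-event reporting sentence covers, and confirm that serious events are recorded for all randomised women.
4. **If one-arm enquiry is intended:** say so, and say that adverse event rates will not be compared between arms.

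The cost is a few minutes per existing visit and one shared set of questions. No extra visits are needed, since all arms already attend.

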### Process evaluation

A process evaluation will be performed to investigate whether the intervention was implemented as planned and whether participants were satisfied with the intervention. The process evaluation will follow Steckler and Linnan’s framework [38]. This will explore:

1) Context (environmental, socio-economic, political factors)

2) Reach (proportion of target population that participates in the intervention)

3) Dose delivered and dose received (proportion of intervention received)

4) Fidelity (extent to which the intervention was delivered as prescribed by the protocol)

5) Acceptability (if intervention materials and advice were well received by the participants)

Qualitative, semi-structured interviews will be conducted to capture the women’s perceptions and experiences of the study. Women will be recruited (*n*=15, 5 per group) after the intervention has been provided. The interviews will be recorded and transcribed.

### Trial outcomes

#### Primary feasibility outcomes

Trial feasibility will include examination of recruitment, retention, intervention adherence, determination of sample size and acceptability. Recruitment will be determined by calculating the proportion of randomised participants from those screened for eligibility. Retention will be measured by the percentage of participants completing the study through the post-assessment. Intervention attendance will be assessed as the number of diet and physical activity sessions completed, with a range of 0 to 8. Adherence to metformin will be defined as participants taking 80% of the study prescribed medication during the trial as assessed by tablet count. The accelerometer wear time will be reported (hours/day). CGM adherence will be defined by sensor wear ≥ 70%. For future full-scale RCTs using CGM, the sample size will be calculated based on the best estimate of the standard deviation and distribution of mean 24-h glucose as determined in the pilot to detect a 0.5-mmol/L difference between arms. Intervention acceptability will be evaluated by an embedded process evaluation using qualitative research methods. Interview questions will address intervention satisfaction and usefulness in addition to ease of using study devices. Additional questions will address the women’s perceptions of risk and benefits of taking metformin, barriers to adherence and the dose of metformin that is acceptable to women. Feedback on the content of the diet and physical activity components will also be obtained in addition to the delivery format (online delivery and time involved).

#### Secondary patient-centred outcomes

A reduction in mean glucose/24h of 0.5 mmol/L after 8 weeks of treatment compared to the standard arm as assessed using CGM.Other glycaemic parameters after 8 weeks of treatment; mean daytime glucose 0.700–23.00h, mean nocturnal glucose 23.00–0.700h, percentage time in tight glucose control target 3.5–6.7mmol/L, percentage time in recommended glucose control target 3.5–7.8mmol/L, area under the curve (AUC) <6.7mmol/L, AUC <7.8mmol/L, glucose variability measures (standard deviation (SD), coefficient of variation (CV)), high blood glucose index (HBGI) and low blood glucose index (LBGI).GDM diagnosis at 24–28 weeks (in accordance with IADPSG and NICE criteria).Metabolome; a targeted high-throughput nuclear magnetic resonance (NMR) metabolomic platform (http://computationalmedicine.fi/) will be used to measure metabolites from blood samples at baseline and at the time of the diagnostic OGTT. The platform quantifies lipid measures including lipoprotein particles (VLDL subdivided into 6 subclasses, IDL, LDL subdivided into 3 subclasses and HDL subdivided into 4 subclasses), constituents within each lipoprotein particle type (triglycerides, total cholesterol, free cholesterol and cholesterol ester levels and phospholipid concentrations), fatty acids, amino acids, glycolysis related metabolites, ketone bodies and inflammatory markers.Dietary intake and physical activity, including changes in GI, GL, saturated fat, time spent in light and moderate exercise and sedentary behaviour from baseline and after the 8-week intervention.

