### Statistical analysis

An intention-to-treat analysis will be completed for participants in all arms. Demographic characteristics will be compared between groups using Student’s *t* test or Mann–Whitney tests for continuous data and Pearson’s chi-squared test for categorical data as appropriate. For continuous variables, results will be presented as means and standard deviations. The number and percentage will be presented for categorical and binary variables. Following distributional checks, log transformations will be carried out as needed. For the primary and main secondary glycaemic outcomes, an adjustment will be made using multiple linear regression (method analysis of covariance; ANCOVA [42]). For yes/no outcomes, binomial regression will be used with a log link to give risk ratios. For other outcomes, where there is no baseline value, adjustment will be made for the primary outcome only. Analytes measured from a targeted NMR metabolome will be checked for normality; those with non-parametric distribution will be log-transformed. Analyte data at baseline and at the time of the diagnostic OGTT (24–28 weeks) will be compared between women who received the intervention and those who did not. To test for the effect of the intervention on dietary and physical activity outcomes, ANCOVA will be used adjusted for trial entry measurements.

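### The two CGM area-under-the-curve outcomes are printed as area below the upper target limits (<6.7 and <7.8 mmol/L), so as written they do not measure glucose exposure above target

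*Protocol article*

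**What the plan says.** The list of glycaemic parameters under Secondary patient-centred outcomes in the Protocol article includes "area under the curve (AUC) <6.7mmol/L, AUC <7.8mmol/L". Just before it, the same list gives "percentage time in tight glucose control target 3.5–6.7mmol/L, percentage time in recommended glucose control target 3.5–7.8mmol/L". The two AUC limits are therefore the upper ends of the tight and recommended ranges, and both carry a less-than sign.

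The wanted direction for glucose is stated for the leading secondary outcome: "A reduction in mean glucose/24h of 0.5 mmol/L after 8 weeks of treatment compared to the standard arm as assessed using CGM". The list also contains daytime and nocturnal mean glucose, SD, CV, HBGI and LBGI. No area above either limit appears anywhere in the article. Under Statistical analysis, the plan is: "For the primary and main secondary glycaemic outcomes, an adjustment will be made using multiple linear regression". The article does not say which way an AUC should move to count as benefit.

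**The concern.** With an upper target limit, the quantity of interest is normally how far and how long glucose runs above it. The printed sign points to the other side of the limit. Glucose below 6.7 or 7.8 mmol/L mixes in-range and low values, and the high excursions that the interventions are meant to reduce are omitted or truncated.

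Two listed outcomes could then be reported with no clear meaning, or could move against the other CGM measures. The Discussion makes the next trial depend on this one proving effective, and the sample size section plans about 20 women per arm. Readers will probably look at the pattern across the CGM measures, and two uninterpretable entries would blur it. A sign corrected only after the data are seen would also look like a post hoc change of outcome.

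**Working it through.** The article gives no figure for these outcomes, so there is none to reproduce. The check scores example days on each reasonable reading of the printed sign.

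**Inputs from the article:** limits T = 6.7 and 7.8 mmol/L; lower range bound 3.5 mmol/L; lower mean glucose is the intended benefit.

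**Assumed:** the glucose profiles. They are illustrations, not trial data.

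**Formulas** (g = glucose, dt = time step, summed over 24 h):
- (a) sum below the limit: Σ g·dt over readings with g < T
- (b) capped at the limit: Σ min(g, T)·dt
- (c) gap below the limit: Σ max(T − g, 0)·dt
- (d) comparator, area above the limit: Σ max(g − T, 0)·dt

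**Results for T = 7.8 (mmol/L·h):**

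| Day | Mean | (a) | (b) | (c) | (d) |
|---|---|---|---|---|---|
| A: 24 h at 5.5 | 5.5 | 132.0 | 132.0 | 55.2 | 0 |
| B: 18 h at 5.5, 6 h at 9.0 | 6.375 | 99.0 | 145.8 | 41.4 | 7.2 |
| C: 18 h at 5.5, 6 h at 12.0 | 7.125 | 99.0 | 145.8 | 41.4 | 25.2 |
| D: 24 h at 7.0 | 7.0 | 168.0 | 168.0 | 19.2 | 0 |
| E: 24 h at 3.0 | 3.0 | 72.0 | 72.0 | 115.2 | 0 |

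For day B: (a) 18 × 5.5 = 99.0; (b) 99.0 + 6 × 7.8 = 145.8; (c) 18 × 2.3 = 41.4; (d) 6 × 1.2 = 7.2. For day C, (d) is 6 × 4.2 = 25.2.

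**Reading (a).** If lower is better, B beats A by 25% (99/132 = 0.75) although its mean is higher. If higher is better, D (168) beats A (132) although its mean is 1.5 mmol/L higher. Neither direction works. For T = 6.7, day D scores 0 because every reading is above the limit, so a move from A to D raises one outcome (132 to 168) and lowers the other (132 to 0).

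**Reading (b).** A and B are ordered correctly if lower is better (132.0 v 145.8). The total area differs by 153 − 132 = 21.0. The cap keeps 13.8 of this and drops 7.2, which is exactly the excess above the limit.

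**Reading (c).** If higher is better, A and B are ordered correctly (55.2 v 41.4). But E, wholly below the trial's 3.5 bound, scores best of all (115.2). Since (b) = 24T − (c), reading (b) with lower as better favours E in the same way.

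**All three readings** give B and C the same score, although C's excess is 3.5 times as large (25.2 v 7.2). Only (d) separates them.

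**Less artificial profiles.** The reference is a base of 5.0 with three meal peaks of +2.0, at 5-minute steps (mean 5.63).
- Lowering the whole curve by 0.5 brings time in 3.5–6.7 from 86.5% to 100%. On reading (a), the <6.7 outcome rises from 112.6 to 123.0 while the <7.8 outcome falls from 135.0 to 123.0.
- Raising it by 0.5 moves them to 102.1 and 147.0, again in opposite directions.
- Doubling the peaks to +4.0 lowers both, to 87.2 and 105.2. Area above rises from 0.7 to 11.0 (T = 6.7) and from 0.0 to 3.9 (T = 7.8).

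**The case against.** The article gives neither a formula nor a direction of benefit, and a condensed article may leave both to the full protocol or analysis plan. The comparison of A with B misleads only if readings below the limit are summed and lower is taken as better. With capping, or with the gap or the sum read as higher-is-better, the same two days are ordered correctly. A reader might infer that hyperglycaemic time is excluded outright, or that the outcomes will point the wrong way. The document does not support that: a capped area still counts such time, at the limit value, and no direction is fixed. This part of the objection stands.

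The sign may also be a plain misprint. The same list prints clock times as 0.700 where 07.00 must be meant. That is likely, but the text cannot settle it.

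Nor do these outcomes drive anything large. The sample size section treats mean 24-h glucose as the main outcome, the future sample size is to be calculated from its SD, and no progression criterion names an AUC. This stands too.

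What does not stand is that the point is only missing detail. The article prints a limit and a side of it. No reading of that side measures the excess above target. An analysis plan that follows the article inherits the problem; one that reverses the sign departs from the published outcome.

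**Conclusion.** The point holds in a limited form. As printed, the two AUC outcomes do not measure glucose exposure above target under any of the three readings. The literal sum below the limit has no consistent direction of benefit; capping drops the excess; the gap rewards ever lower glucose. A reversed inequality is the probable cause, not an established one.

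The numbers rest on assumed profiles. They show that mis-ranking can happen, not how often it would in this trial. A reader might go further and infer that the trial cannot detect an effect on high glucose, or that the decision on the next trial is compromised. The article does not support this: mean 24-h, daytime and nocturnal glucose, time in both target ranges and HBGI all register hyperglycaemia, and planning of the next sample size does not use the AUC. The effect is confined to two of several secondary outcomes in a pilot, but it should be corrected before analysis.

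**What to change.** Confirm which side of the limits was intended. If area above was meant, restate the two outcomes as area above 6.7 mmol/L and area above 7.8 mmol/L, Σ max(g − T, 0)·dt, with lower as better. Raising glucose at any time can never lower this quantity. Scaling for sensor wear time can stay in the analysis plan.

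If area below the limits was truly intended, drop both outcomes: mean glucose, time in target and LBGI already cover that information.

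The cost is two inequality signs and a one-line definition, dated before the CGM data are analysed. The sensors, visits, data and sample size do not change.

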### Sample size calculation and loss to follow-up

The study is intended as a pilot, one of whose aims is to gather the information needed for planning the definitive trial. This includes estimating the SD of the main outcome (the difference in mean 24-h glucose between arms) and checking the distribution. With twenty participants per arm, the SD can be estimated to within 80% of the true value. A 0.5mmol/L difference in mean 24-h glucose was considered to be of biological relevance based on data from comparable studies of CGM in pregnant women with obesity [39–41]. To account for up to 25% loss to follow-up and achieve a total sample size of 60, a sample of 84 women will be recruited.

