**Methods:**

Women aged 18 years or older with a singleton pregnancy and body mass index (BMI) ≥ 30kg/m^2^ will be recruited from one maternity unit in London, UK. The risk of GDM will be assessed using a multivariable GDM prediction model combining maternal age, mid-arm circumference, systolic blood pressure, glucose, triglycerides and HbA1c. Women identified at a higher risk of developing GDM will be randomly allocated to one of two intervention groups (lifestyle advice with or without metformin) or standard antenatal care. The primary feasibility outcomes are study recruitment, retention rate and intervention adherence and to collect information needed for the sample size calculation for the definitive trial. A process evaluation will assess the acceptability of study processes and procedures to women. Secondary patient-centred outcomes include a reduction in mean glucose/24h of 0.5mmol/l as assessed by continuous glucose monitoring and changes in a targeted maternal metabolome, dietary intake and physical activity. A sample of 60 high-risk women is required.

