#### 13–15^+6^ weeks’ gestation appointment: baseline and randomisation

At the first appointment, informed consent will be obtained by the chief investigator from women to be randomised into the trial. All participants will be fitted with a glucose sensor (Dexcom G6) to be worn for 7–10 days. The sensors are small, easy to wear, waterproof devices which require no finger prick calibration. The sensors will be applied to the back of the upper arm or abdomen of the participant and activated in blinded mode. To assess dietary intake, a semi-quantitative food frequency questionnaire (FFQ) will be administered to evaluate dietary glycaemic load (GL), glycaemic index (GI), saturated fat and other dietary variables [34]. Physical activity will be assessed by Axivity accelerometer AX3 (https://axivity.com/product/ax3).

Following the baseline assessment, randomisation will be performed electronically by the research team via a secure online-based data management platform (MedSciNet™) in order to conceal the sequence until interventions are assigned. Women will be randomised (1:1:1) into three groups:

a. Lifestyle advice

b. Lifestyle advice plus metformin

c. Standard antenatal care

The randomisation schedule will be minimised according to ethnicity (Black, White, Asian, Other), BMI (30−34.9kg/m^2^, 35−39.9kg/m^2^, ≥40kg/m^2^), parity (nulliparous/multiparous) and age. Participants will be allocated sequential study numbers regardless of allocation to the intervention or standard care group. Due to the nature of the study design, it will not be possible to blind participants or research staff to the randomisation arm.

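### Two sample-size figures do not hold as written: 25% loss on 60 gives 80 or 81 women, not 84, and the SD precision claim lacks a confidence level and a pooling rule

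*Protocol article*

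**What the plan says.** The protocol article, section *Sample size calculation and loss to follow-up*, gives the SD as one reason for the pilot's size: "With twenty participants per arm, the SD can be estimated to within 80% of the true value". No confidence level is attached, and nothing says whether the SD is that of one arm or is pooled over arms. The same section describes the aim as "estimating the SD of the main outcome (the difference in mean 24-h glucose between arms".

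The recruitment target follows in one sentence: "To account for up to 25% loss to follow-up and achieve a total sample size of 60, a sample of 84 women will be recruited". The abstract repeats the analysable target: "A sample of 60 high-risk women is required". Allocation is equal over three arms ("Women will be randomised (1:1:1) into three groups"). No other part of the article gives a further reason for 84.

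The section *Primary feasibility outcomes* says how the SD will be used. Future full-scale trials with continuous glucose monitoring will be sized to detect 0.5 mmol/L, "based on the best estimate of the standard deviation and distribution of mean 24-h glucose as determined in the pilot".

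**The concern.** The loss rate, the analysable target and the recruitment target stand in one sentence, so each should follow from the other two. They do not. Recruitment and retention are primary feasibility outcomes here, so the figures against which they are read should be consistent.

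The precision sentence is the only quantitative justification for 20 per arm, and determining the sample size of a later trial is a primary feasibility outcome. As worded, the sentence cannot be checked. Its meaning changes with the interpretation of 80%, with the confidence level and with pooling, and these choices give clearly different precision.

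The parenthesis adds a smaller difficulty. In a parallel-group trial a difference between arms has no SD across individual women. The quantity needed for planning is the between-woman SD of mean 24-h glucose.

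**Working it through.** **Recruitment target.** Inputs from the sample-size section: 60 analysable women, 25% loss, 84 recruited. From the randomisation section: three equal arms.

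- Standard inflation, N/(1 − d): 60/0.75 = 80.
- The same per arm, rounded up: 20/0.75 = 26.7, so 27 per arm and 27 × 3 = 81.
- The common shortcut, N × (1 + d): 60 × 1.25 = 75.

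None gives 84. Working backwards from 84:

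- Loss that leaves 60: 1 − 60/84 = 0.286, or 28.6%.
- Completers at 25% loss: 84 × 0.75 = 63, or 21 per arm.

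The stated figure therefore exceeds its basis by 84 − 81 = 3 or 84 − 80 = 4 women.

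**Precision of the SD.** Input: 20 women per arm. Assumption: normal data with a common SD, σ. For an estimate s on df degrees of freedom, df × s²/σ² follows a chi-square distribution on df. One arm has df = 20 − 1 = 19, two arms pooled have 2 × 19 = 38, and three arms pooled have 3 × 19 = 57. F below is the chi-square distribution function.

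*Literal reading, ±80%:* P(0.2 < s/σ < 1.8) = F(3.24 df) − F(0.04 df). Even for one arm this exceeds 0.9999, so the statement is true but uninformative.

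*Read as ±20%:* P(0.8 < s/σ < 1.2) = F(1.44 df) − F(0.64 df). The 95% confidence interval for σ runs from s√(df/χ²₀.₉₇₅) to s√(df/χ²₀.₀₂₅).

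| SD from | df | P(within ±20%) | 95% CI for σ, as a multiple of s |
|---|---|---|---|
| one arm of 20 | 19 | 0.782 | 0.76 to 1.46 |
| two arms pooled | 38 | 0.920 | 0.82 to 1.29 |
| three arms pooled | 57 | 0.968 | 0.85 to 1.22 |

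To be within ±20% with 95% probability takes 49 women in a single arm, 25 per arm with two arms pooled, or 17 per arm with three pooled. Twenty per arm meets that standard only when all three arms are pooled.

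*Read as ±20% with 80% confidence:* the central 80% range of s/σ for one arm is 0.783 to 1.197, so 20 women come close but do not quite reach it.

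**Which SD.** The sample-size section attaches the SD to the difference between arms; *Primary feasibility outcomes* attaches it to mean 24-h glucose itself. The second is the usable quantity. The two sections need the same wording.

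**The case against.** The strongest reply is that the defects lie in the wording and that the design is sound. Much of it stands.

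- *Pooling is a natural reading.* The article refers to a single SD and plans analysis of covariance for the glycaemic outcomes, which assumes one common residual SD. On that reading 20 per arm gives ±20% with 97% probability. A reader might infer from the sentence that the pilot is too small to estimate the SD usefully; the pooled result contradicts this.
- *The right quantity is already named.* *Primary feasibility outcomes* bases future sizing on the SD of mean 24-h glucose. A reader might infer from the parenthesis that a later trial would be planned on the wrong SD, but the operative sentence does not support that.
- *The recruitment discrepancy is harmless in direction.* At the stated maximum loss, 84 still delivers the 60 required.
- *Underpowering does not follow.* A reader might infer that a definitive trial sized on the point estimate is more likely than not to be underpowered. If it is planned at 80% power on the pooled SD (57 df), true power falls below 80% in 52% of pilots, but median realised power is 79.5% and the mean is 78.9%. About 12% of pilots would lead to power below 70%, which is a tail risk for the later trial's own protocol to handle. A best estimate does not rule out an allowance for uncertainty, and sizing on an upper limit is one debatable option. The Discussion also foresees a next trial powered on GDM prevalence, a binary outcome not sized on this SD.

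The reply leaves two things unanswered. No standard calculation turns 60 and 25% into 84, and allowing for losses of at most 25% does not help, since smaller losses need fewer women. The article also never states the pooled, ±20% reading that makes the precision claim informative.

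**Conclusion.** The point holds and is minor. The recruitment figure is three to four women above what its stated inputs give, on the safe side. The precision sentence cannot be interpreted as written: depending on an unstated choice, the probability of being within ±20% is 78% or 97%.

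This rests on three assumptions: normally distributed mean 24-h glucose, a common SD across arms, and ±20% as the intended meaning. The article states none of the three. Taking the residual SD after adjustment for one baseline covariate would leave 56 df and hardly change the result (probability 0.966, 95% CI 0.844 to 1.227 times the estimate).

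The finding does not show that the pilot is too small, that its analysis is affected, or that a later trial would be underpowered.

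**What to change.** In *Sample size calculation and loss to follow-up*:

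1. Either restate the recruitment target as 81 (27 per arm), or keep 84 (28 per arm) and state that it allows for about 28% loss.
2. Replace the precision sentence with: *With 20 analysable women per arm, the between-woman SD of mean 24-h glucose, pooled within the three arms (57 df), lies within 20% of the true value with about 97% probability (normal data assumed).*
3. Reword the parenthesis so that the SD is that of mean 24-h glucose, matching *Primary feasibility outcomes*.

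The cost is wording only. No additional women are needed, and neither the design nor the analysis changes.
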